# The impact of session-introducing mindfulness and relaxation interventions in individual psychotherapy for children and adolescents: a randomized controlled trial (MARS-CA)

**DOI:** 10.1186/s13063-022-06212-0

**Published:** 2022-04-11

**Keywords:** Mindfulness, Relaxation, Component study, Therapeutic alliance, Randomized controlled trial, Children, Adolescents

## Abstract

**Background:**

The investigation of mindfulness-based interventions (MBIs) in cognitive-behavioral therapy has greatly increased over the past years. However, most MBI research with youth focuses on structured, manualized group programs, conducted in school settings. Knowledge about the implementation and effects of MBIs in individual psychotherapy with children and adolescents is scarce. To fill this research gap, the “Mindfulness and Relaxation Study – Children and Adolescents” (MARS-CA) is designed. It aims to assess the effects of short session-introducing interventions with mindfulness elements on juvenile patients’ symptomatic outcome and therapeutic alliance in individual child and adolescent psychotherapy.

**Methods:**

MARS-CA is conducted at a university outpatient training center for cognitive-behavior therapy. Short session-introducing interventions with mindfulness elements will be compared to short session-introducing relaxation interventions and no session-introducing intervention to explore their effects on symptomatic outcome and therapeutic alliance. The session-introducing interventions will take place at the beginning of 24 subsequent therapy sessions. We hypothesize that patients’ symptomatic outcome and therapeutic alliance improve more strongly in the mindfulness condition than in the other two conditions and that the mindfulness condition moderates the relationship between therapeutic alliance and symptomatic outcome. Patients and their trainee therapists will be randomized to one of the three treatment arms. Participants aged between 11 and 19 years and having a primary diagnosis of either a depressive disorder, an anxiety disorder, or a hyperkinetic disorder will be included. Therapeutic alliance will be assessed after every therapy session (therapy session 1 to therapy session 24), symptomatic outcome will be assessed before the start of treatment (pre), after the 3rd, the 10th, and the 17th therapy sessions, at the end of treatment (24th therapy session, post), and at a 6-month follow-up. Additionally, mindfulness and mindfulness-related measures as well as demographic data, adherence, allegiance, and therapeutic techniques will be assessed. It is our aim to assess a sample of 135 patients. We will conduct multilevel modeling to address the nested data structure.

**Discussion:**

The study can provide information about how add-on MBIs, conducted by trainee therapists, influence therapeutic alliance and symptomatic outcome in individual psychotherapy in children and adolescents.

**Trial registration:**

ClinicalTrials.gov NCT04034576. Registered on July 17, 2019

## Administrative information

Note: the numbers in curly brackets in this protocol refer to SPIRIT checklist item numbers. The order of the items has been modified to group similar items (see http://www.equator-network.org/reporting-guidelines/spirit-2013-statement-defining-standard-protocol-items-for-clinical-trials/).

## Introduction

### Background and rationale {6a}

Mindfulness has its origins in Eastern—mostly Buddhist—traditions and can be conceptualized as a specific form of attention that is non-judgmental, purposeful, and focused on the present moment [1].

This state of being aware of one’s own experiences in the here and now without being judgmental may support the disengagement from perseverating cognitive activities and the enhancement of effective emotion regulation [2]. It is thus reasonable to expect that patients with mental disorders may largely benefit from mindfulness. Therefore, mindfulness is currently being hyped in clinical psychology, with over 600 publications in scientific journals per year [3]. Evidence for the positive effects of mindfulness-based interventions (MBIs) in group settings on outcome measures of various mental disorders have been provided by a number of meta-analyses ( [4–7]; effect sizes from pre–post –follow-up–designs: *g* = 0.31–0.63 [4–6], effect sizes in contrast to other comparison groups (evidence-based treatment to no treatment/waitlist controls): *d* = − 0.004–0.55 [7], *g* = − 0.07–0.53 [5]). However, the most common form of psychotherapy is individual therapy. Empirical evidence on mindfulness in individual therapy is scarce and restricted to adult populations [8, 9]. Therefore, it remains unclear if mindfulness improves individual psychotherapy with children and adolescents.

In the following sections, we will delineate current applications of mindfulness in adult psychotherapy, in child and adolescent psychotherapy, and in individual psychotherapy. Furthermore, we will describe the impact of therapeutic alliance and mindfulness practice on treatment outcome in children and adolescents.

### Application of mindfulness in psychotherapy

The most prominent applications of MBIs are “mindfulness-based stress reduction” (MBSR; [1]) and “mindfulness-based cognitive therapy” (MBCT; [10]). These group programs consist of several elements such as psychoeducation, different mindfulness interventions (e.g., body scan, mindful walking, breathing space), and general group-related factors [11]. Until now, it is still unclear if the mindfulness interventions of these group programs are the crucial element for patients’ symptom improvement. Current studies that compare groups of patients who have participated in the whole MBCT program to groups who have taken part in the MBCT program without the mindfulness elements provide ambiguous results [11–14]. Only a few studies have compared MBIs with active control groups in clinical settings (e.g., [12, 15]), although the comparison to conventional psychotherapeutic methods is crucial to demonstrate the potential impact of MBIs on clinical populations.

### Application of mindfulness programs in child and adolescent psychotherapy

With regard to younger age groups, both MBSR and MBCT have been adapted for children (e.g.‚ A Still Quiet Place: A Mindfulness Program for Teaching Children and Adolescents to Ease Stress and Difficult Emotions’ [16], Learning to Breathe [17], MBCT for Anxious Children (MBCT-C; [18]). Additionally, multiple other programs with mindfulness elements for children and adolescents have been created [19]. Most of these have been developed for application in school settings and all of these are group programs. With regard to children and adolescents with mental disorders, the most prominent mindfulness program is the MBCT-C program [18]. It consists of 12 sessions with 6 to 8 children, each session lasting 90 min. Sessions are composed of a combination of cognitive therapy and mindfulness interventions [18]. Beside the MBCT-C program, which is primarily designed for children with internalizing disorders, further MBCT adaptations are created for children and adolescents with other mental disorders (e.g., the MYMind program for children with attention-deficit/hyperactivity disorder (ADHD) and autism-spectrum disorder (ASD): 9 sessions with 90 min each session, 4 to 6 adolescent participants; [20–22]).

In sum, to the authors’ knowledge, all existing mindfulness programs for children and adolescents are group programs. Although there exist some adaptations for children and adolescents with mental disorders, the main delivery setting of mindfulness programs in youth are schools.

Meta-analyses including both non-clinical and clinical samples revealed small-to-moderate effect sizes (Becker’s del, a measure for the difference of pre-post effect sizes = 0.2–0.5; *g* = 0.305–0.462) of MBIs on treatment effects [4, 23]. A meta-analysis focused on both clinical and non-clinical randomized trials [24], revealing small positive effects of MBIs on mindfulness, executive functioning, attention, depression, anxiety/stress, and negative behavior (*d* ranging 0.16–0.30; [24]). Taking only RCTs with active control treatments into account reduced the number of significant areas with positive effect sizes to mindfulness (*d* = 0.42), depression (*d* = 0.47), and anxiety/stress (*d* = 0.18) [24]. However, the effect sizes in these areas increased from small effect sizes to moderate effect sizes (with the exception of anxiety/stress), indicating that MBIs are more effective than other treatments [24]. It should be noted that the studies with an active control condition included in this meta-analysis have not been conducted in a clinical setting.

### Mindfulness in individual psychotherapy

Many clinicians apply mindfulness interventions in individual therapy [9] and have already done so during their training [25]. Typically, they apply only single mindfulness interventions and not the whole MBSR/MBCT package [9, 26, 27]. Generally speaking, empirical evidence of mindfulness in individual therapy is scarce and results are contradictory, with some studies showing positive effects on outcome measures [28, 29] and a longitudinal study demonstrating no positive effects [30]. A meta-analysis showed that mindfulness interventions as a stand-alone intervention have beneficial effects on anxiety and depression in healthy subjects [31], thus indicating that mindfulness is potentially an effective add-on in individual therapy.

Furthermore, mindfulness practice may have an impact on other variables, such as therapeutic alliance, which will be elaborated in the next section.

### Impact of therapeutic alliance and mindfulness practice on treatment outcome in children and adolescents

Meta-analyses show that therapeutic alliance is positively related to treatment outcome in child and adolescent therapy, with an effect size of *r* = .14 and *r* = .19, respectively [32, 33]. Hence, it is of clinical importance to find methods to strengthen the therapeutic alliance, which in turn could strengthen symptomatic outcome. One possibility to strengthen symptomatic outcome through therapeutic alliance is to practice mindfulness [34], preferably by both therapist and patient [27]. By practicing mindfulness, the transition from stressful daily life to elevated presence in the therapy session is improved, the conversations between therapist and patient are simplified, and the whole therapeutic process is calmed down [27], which may all contribute to improve therapeutic alliance between therapist and patient. Additionally, on the therapists’ side, mindfulness practice enhances self-acceptance and, consequently, improves acceptance and empathy to others (according to the two-stage model of Kristeller and Johnson [35]). Furthermore, therapists’ practice of focusing the attention on the present moment via mindfulness can also increase alliance, as a stronger attention focus on patients is possible.

### Aim of the present study

Summarizing the previous findings, single mindfulness interventions are already frequently implemented in individual psychotherapy with adult patients [9]. However, empirical evidence is scarce [15, 28, 29], and, to the authors’ knowledge, nothing is known about the effects of single mindfulness interventions in child and adolescent psychotherapy. Additionally, there is only limited knowledge about the (non-)superiority of mindfulness interventions to other interventions such as relaxation exercises [15]. To close this research gap, the present study aims (a) to investigate the effects of single mindfulness interventions on symptomatic outcome and therapeutic alliance and (b) to compare the effects of mindfulness interventions to other, already established interventions in individual child and adolescent psychotherapy.

### Objectives {7}

The main purpose of the study is to investigate whether session-introducing mindfulness interventions (SIMI) in comparison to session-introducing relaxation interventions (SIRI) and no specific intervention at the beginning of individual psychotherapy sessions with children and adolescents between 11 and 19 years of age have a positive impact on the therapeutic process. Session-introducing intervention means that in the first 5 to 10 min of a 50-min therapy session, either a short mindfulness intervention, or a short relaxation intervention, or no specific intervention (but the proceeding as usual) will be conducted. This session-introducing intervention could foster self-acceptance and help to focus attention on the present moment of the session, therefore strengthening the therapeutic alliance and outcome effects. Specifically, we want to investigate if SIMI in comparison to SIRI and no intervention at the beginning of psychotherapy sessions lead to a reduction in psychopathological symptomatology and to an improvement of the therapeutic alliance. Furthermore, we hypothesize that the mindfulness condition moderates the relationship between therapeutic alliance and symptomatic outcome. Before the start of therapeutic treatment, patients will be randomized either to the intervention group, practicing SIMI at the beginning of the therapy sessions (IG-M), or to the active control group, practicing SIRI at the beginning of the therapy sessions (CG-R), or to the control group with no specific interventions at the beginning of the therapy sessions (CG). We will investigate the following hypotheses:

H1) We hypothesize that patients of the IG-M will improve more in symptomatic outcome in comparison to the CG-R and CG.

H2) We hypothesize that both patients and therapists of the IG-M will experience stronger increases of therapeutic alliance across the course of therapy in comparison to the CG-R and CG.

H3) We hypothesize that the mindfulness condition moderates the relationship between therapeutic alliance and symptomatic outcome.

### Trial design {8}

MARS-CA is a single-center, parallel group, three-arm randomized controlled trial. It is designed to test the effectiveness of SIMI in contrast to SIRI to no specific interventions at the beginning of therapy sessions with children and adolescents. Study participants will be randomized either to the intervention group, practicing SIMI at the beginning of the therapy sessions (IG-M), or to the active control group, practicing SIRI at the beginning of the therapy sessions (CG-R), or to the control group with no specific interventions at the beginning of the therapy sessions (CG). A flow chart through the study is shown in Fig. 1.

**Fig. 1 Fig1:**
[figure not shown]
CONSORT flow chart. ADHD, attention-deficit/hyperactivity disorder; CBT, cognitive-behavioral therapy; CEQ, Credibility/Expectancy Questionnaire; CG, control group CG+R, control group: relaxation; CPP, Center for Psychological Psychotherapy; DISYPS-III; SBB-ADHS, Diagnostic System for Mental Disorders; ADHD Self-Rating Scale; DISYPS-III; SBB-ANG, Diagnostic System for Mental Disorders; Anxiety Self-Rating Scale; SBB-DES, Diagnostic System for Mental Disorders; Depression Self-Rating Scale; FTB-KJ, German Version of the Therapeutic Allegiance Scale for Children; HICBI, Heidelberg Inventory of Cognitive-Behavioral Interventions; IG-M, intervention group: mindfulness; Kinder-DIPS – OA, Diagnostic Interview for Mental Disorders in Children and Adolescents – Open Access KIMS, Kentucky Inventory of Mindfulness Skills; SCS, Self-Compassion Scale; TPI, Therapeutic Presence Inventory; YSR, Youth Self-Report

### Patient involvement in the trial

Juvenile outpatients have assessed all SIMI and SIRI for eligibility prior to the beginning of the trial (65 evaluations from 36 juvenile patients). Subsequently, all SIMI and SIRI have been adapted to the feedback from the patients so that the interventions are appropriate for the implementation in individual psychotherapy with children and adolescents within the trial. No other patient or public involvement has taken place in the presented research design.

## Methods: participants, interventions, and outcomes

### Study setting {9}

The data of MARS-CA will be collected at the outpatient training center for child and adolescent cognitive behavior therapy (CBT) at the Center for Psychological Psychotherapy, Psychological Institute, University of Heidelberg, Germany.

### Eligibility criteria {10}

Inclusion criteria for patients participating in MARS-CA are a primary hyperkinetic disorder, depressive disorder, or anxiety disorder diagnosis. Exclusion criteria for patients are as follows: (a) age below 11 or above 19 years, (b) deficient German language skills, (c) comorbid psychotic disorder, and (d) acute suicidality. Other comorbidities are not considered as an exclusion criterion. Drop-out criteria are (a) termination of individual psychotherapy before the 24th therapy session, (b) refusal to participate in the study any longer, and (c) inability to take part in the interventions any longer (due to severe crises during the therapy process, propensity for dissociation during the interventions, etc.). Trainee therapists who want to take part in the study have to visit two workshops for study preparation.

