#### Intervention description {11a}

Depending on the condition (IG-M vs. CG-R vs. CG), three different SIMI, three different SIRI, or no session-introducing intervention will be conducted. With regard to the SIMI, [name] (JK) and [name] (JM) have composed versions for MARS-CA based on the following interventions: mindful walking, body scan, and breathing space of the MBCT-C program by Semple and Lee [18]. During the mindful walking intervention, patients are asked to pace up and down the therapy room and to perceive their movements with an accepting attitude [18]. In the body scan intervention, patients are expected to perceive one part of the body after another in the here and now with reducing the appraisal of thoughts, emotions, and physical sensations to a minimum. The breathing space intervention is some kind of “mini-meditation” during which the patients firstly become aware of their thoughts, emotions, and physical sensations in the present moment, secondly put their focus solely on their breathing, and thirdly extend their awareness beyond their breathing again [18]. The SIRI comprise a self-developed walking relaxation intervention, an adapted version of the progressive muscle relaxation (PMR) for children [36], and an adapted version of the Captain Nemo imagery journey “dolphin riding” [37]. The self-developed walking relaxation intervention has been designed by the authors, together with a child and adolescent psychotherapist having long-term experience in relaxation exercises. It starts with the patients clapping their hands until they have found an appropriate rhythm. In the next step, patients are asked to further clap their hands and to additionally walk through the therapy room, suitable to the clap rhythm. During the PMR intervention, patients are invited to briefly tense and relax single muscle groups in alternation. The intervention ends in tensing and relaxing of all muscle groups of the body [36]. The imagery journey intervention, an adapted version of the Captain Nemo imagery journey “dolphin riding,” consists of an underwater excursion during which the patients imaginatively meet some friendly dolphins [37].

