#### Criteria for discontinuing or modifying allocated interventions {11b}

Not applicable, no discontinuing or modifying allocated interventions envisaged.

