#### Sample size {14}

A recent meta-analysis has detected small to medium effects of MBIs in RCTs with youth in depression (*d* = 0.27), anxiety (*d* = 0.16), executive functions (*d* = 0.30), and attention (*d* = 0.19) [24]. A meta-analysis that has analyzed the effects of meditation in non-clinical groups of adult meditators has detected moderate effect sizes for meditation compared to relaxation (*r* = .21) on psychological outcomes [43].

Taking these results into account, power analyses with G*Power [44] for the detection of small to medium-sized effects (Cohen’s *f* = 0.12) for the interaction between time (pre, T3, T10, T17, T24) and treatment condition (IG-M vs. CG-R vs. CG) (analysis of variance (ANOVA) repeated measures, within-between-interaction, *α* = 0.05, power (1 − β) = 0.80, number of groups = 3, number of measurements = 5, pre–post correlation *r* = 0.5, nonsphericity correction = 1) for the YSR 11-18R total score primary outcome resulted in a sample size of 108 patients. Although this should only be seen as a proxy for the power of the reported multilevel models (MLMs), previous research showed that power in MLM is often comparable to (or even higher than) power in an ANOVA design [45, 46]. The planned sample size should, therefore, be considered a conservative estimate required to detect a small to medium sized condition × time interaction. Taking a drop-out-rate of about 25% into account (i.e., 27 patients), a total sample of 135 patients will be assigned to one of the three treatment groups by a stratified randomization process.

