#### Implementation {16c}

Patients will be enrolled in the study by the trainee therapists and in consultation with one researcher of the MARS-CA team. Patients will be assigned to one of the three intervention arms by an independent research assistant who is not part of MARS-CA research team.

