### Assignment of interventions: blinding

#### Who will be blinded {17a}

The focus of the current study is on external validity and generalizability of the results to routine clinical practice. Consequently, according to extension of the CONSORT statement concerning the criteria of a pragmatic randomized controlled trial [47, 48], in the current study, no blinding will be implemented.

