#### Plans to promote participant retention and complete follow-up {18b}

Retention of patients and assessment of data will be realized by close collaboration between trainee therapists and MARS-CA research assistants (via personal meetings, phone calls, and e-mail contact). Assessment of data (during active study participation and follow-up) can be executed either online via an online platform [49] or via paper pencil so that data collection is as convenient as possible for all study participants.

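### Drop-out criterion (c) and the harms procedure turn inability to do the session-opening exercise into a study exit, and at least two of its triggers cannot arise in the no-exercise arm

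*Protocol article*

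**What the plan says.** Eligibility criteria {10} lists three drop-out criteria: (a) therapy ends before session 24, (b) the patient refuses further participation, and (c) "inability to take part in the interventions any longer (due to severe crises during the therapy process, propensity for dissociation during the interventions", followed by an open-ended etc.

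Intervention description {11a} sets out what each arm does: "three different SIMI, three different SIRI, or no session-introducing intervention will be conducted". The exercises are delivered in IG-M and CG-R, and CG proceeds as usual.

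The section on discontinuing or modifying allocated interventions {11b} reads "no discontinuing or modifying allocated interventions envisaged". Adverse event reporting and harms {22} has patients report discomfort during the exercises to their therapist, who reports it to the research team. The team then decides whether staying in the study is justifiable. Under Who will be blinded {17a}, "no blinding will be implemented".

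The section on non-adherence and missing data {20c} plans an intention-to-treat (ITT) and a completer analysis. Sample size {14} says: "Taking a drop-out-rate of about 25% into account (i.e., 27 patients), a total sample of 135 patients".

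**The concern.** Criteria (a) and (b) describe events that any patient can have. Criterion (c) concerns a treatment component that one arm lacks. A patient who dissociates during a body scan but stays in therapy, and is willing to fill in questionnaires, is a drop-out in IG-M. In CG the corresponding event cannot happen, so a comparably vulnerable patient who stays in therapy remains in the study. The article describes no middle route: {11b} foresees no stopping of the exercise, and the decision in {22} is about study participation, not the exercise alone.

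Two things are at stake. First, H1 claims superiority of IG-M over CG as well as over CG-R. If completers are the patients who meet no drop-out criterion, selection after randomisation differs between IG-M and CG and is tied to clinical state. Second, if the YSR is no longer collected after such an exit, the ITT analysis loses the later measurements of these patients, and no analysis plan can restore them.

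**Working it through.** **1. Which routes out are open in which arm**

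| Route | IG-M | CG-R | CG |
|---|---|---|---|
| (a) therapy ends before session 24 | yes | yes | yes |
| (b) refusal | yes | yes | yes |
| (c) severe crisis during therapy | yes | yes | open to reading |
| (c) dissociation during an exercise | yes | yes | no |
| {22} discomfort during an exercise, then team decision | yes | yes | no |

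The last two rows are certain from the text. The third is not.

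**2. The plan's own figure.** Inputs from Sample size {14}: f = 0.12, 3 groups, m = 5 measurements, correlation 0.5, alpha 0.05, power 0.80. With lambda = f² × N × m / (1 − rho) = 0.0144 × 108 × 5 / 0.5 = 15.55, and 8 and (108 − 3) × 4 = 420 degrees of freedom, power is 0.808. The smallest adequate N is 107 (power 0.803), and 108 is the next multiple of 3. So 108 reproduces. Then 135 − 27 = 108, and 108/3 = 36 completers per arm.

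**3. Illustration of the completer shift.** The article gives no rate for (c), and the 27 expected drop-outs cover all reasons. Assume k further IG-M patients removed under (c), none in CG, and removed patients D SD worse on the YSR at session 24. The shift in the IG-M completer mean is k/(36 + k) × D:
- k = 0: 0
- k = 1, D = 0.5: 1/37 × 0.5 = 0.01 SD
- k = 2, D = 1: 2/38 = 0.05 SD
- k = 4, D = 1: 4/40 = 0.10 SD

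D = 0 gives no bias, and a negative D reverses it.

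**4. A second illustration.** Assume that a share q of IG-M with the worst latent course is removed, that this course correlates r with outcome, and that the true effect is zero. The spurious benefit is r × φ(c)/(1 − q), where φ is the standard normal density and c its 1 − q quantile. For r from 0.3 to 1.0, with the two-sided type I error of a simple contrast (nominal 0.05):
- q = 2%: 0.015 to 0.049 SD, error 0.050 to 0.055
- q = 5%: 0.033 to 0.109 SD, error 0.052 to 0.074
- q = 10%: 0.058 to 0.195 SD, error 0.057 to 0.127

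**5. Yardsticks.** Sample size {14} cites d = 0.16 to 0.30. If IG-M diverges linearly from two equal control arms, f² = delta² × 2/9 × time variance. For sessions 0, 3, 10, 17 and 24 scaled to 0–1 the time variance is 0.1357, so delta = 0.12/√(0.2222 × 0.1357) = 0.69 SD at session 24. A 36 versus 36 contrast has standard error √(2/36) = 0.24 SD.

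**6. ITT data at risk, only if collection stops at exit.** Of the five treatment-phase YSR points (pre, S3, S10, S17, S24), leaving between S3 and S10 loses 3, between S10 and S17 loses 2, and between S17 and S24 loses 1, plus follow-up each time.

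**The case against.** The strongest case against has four parts.

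*The reading is not settled.* A reader might infer that criterion (c) as a whole can be met only in the exercise arms. The text does not support that. A severe crisis is not specific to an exercise, Implementation {16c} says "Patients will be assigned to one of the three intervention arms", and the Conclusion counts the passive condition as a control intervention. This stands, and it limits the certain asymmetry to dissociation and discomfort during an exercise.

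*ITT covers the main risk.* It is planned, and the multilevel model can use whatever a patient provided before leaving. A reader might infer from 135 − 27 = 108 that drop-outs give no further data, but that is ordinary drop-out inflation and weak evidence. This stands as far as the article goes: ITT is harmed only if collection stops, which is not stated.

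*Definitions belong elsewhere.* Defining completers, ranking the two analyses and reporting exits by arm are commonly left to a statistical analysis plan. Agreed, and none of that is held against this protocol. The drop-out rule is different, because the protocol states it and it governs which data exist.

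*The size is assumed and mismatched.* The shift in step 3 concerns the session-24 mean, whereas the primary test is group by time. If removed patients are also worse at baseline, part of the shift cancels. Even uncorrected, 0.10 SD is about 14% of 0.69 SD and less than half of one standard error. This also stands.

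Only an exercise arm can have exercise intolerance, so the asymmetry in stopping the exercise is unavoidable. What can be avoided is turning it into a study exit.

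**Conclusion.** The point holds in a limited form. Criterion (c) and the harms procedure make inability to do the exercise a reason to leave the study, and at least two triggers have no counterpart in CG. This can selectively bias the completer contrast of IG-M with CG, provided completers are those who meet no drop-out criterion. IG-M versus CG-R is largely protected, because both arms have exercises of matched length and the same rule. It is affected only if intolerance differs between the two sets of exercises.

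A reader might infer that the bias favours IG-M. That needs removed patients to have a worse course, which is plausible but not documented. A reader might also infer a bias as large as the effects sought. Under the second illustration, the range cited in the sample size section is reached only when about 10% or more of IG-M is removed and removal is strongly related to outcome. At 2% it is negligible. The document fixes neither size nor direction. This is a cheap improvement, not a threat to the trial's main conclusion.

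**What to change.** Amend three sections together:
- **Eligibility criteria {10}:** delete (c) as a drop-out criterion and record stopping the exercise as non-adherence. Apply (a) and (b) identically in all three arms.
- **{11b}:** state that the exercise may be stopped while the patient stays in the trial.
- **{22}:** let the safety decision stop the exercise only, at once if needed.

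Unless consent is withdrawn, continue the YSR up to session 24 and the 6-month follow-up. The route already exists under {18b}: "Assessment of data (during active study participation and follow-up) can be executed either online via an online platform" or on paper.

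The cost is amendment wording, ethics approval and a few extra reminders by the research assistants. The real downside is burden on patients in crisis, who may decline. The full patient survey takes 45–50 minutes, but the YSR alone takes 15–20, so it could be requested on its own. Recruitment has run since April 2019, so patients before and after the change would fall under different rules, and the date of the change should be recorded.
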